#### Health-economic evaluation

Following the CHEERS statement [29], the health-economic evaluation will be conducted in agreement with the ITT principle on a wide dataset, which will be multiply imputed using chained equations. For the health-economic evaluation, we will take both the healthcare systems perspective and the societal perspective, thus incorporating the intervention costs, all other healthcare costs, the patients’ (and their families’) out-of-pocket costs into account in the healthcare perspective, plus productivity losses (stemming from absenteeism and lesser productivity while at work but feeling ill) for the societal perspective.

In the *cost-effectiveness analyses* incremental costs will be related to (a) IDS-SR treatment response, (b) IDS-SR remission, while in a *cost-utility analysis* the incremental costs will be related to EQ-5D-5L quality adjusted life year (QALY) gained.

To that end, incremental cost-effectiveness ratios (ICERs) will be computed, bootstrapped (2500 times) and the bootstrapped ICERs will be projected on the ICER plane as a scatter of simulated ICERs. When the simulated ICERs largely fall in the NE quadrant of the ICER plane, then the intervention generates better health outcomes than enhanced usual care, albeit for additional costs; in the NW quadrant the intervention costs more than enhanced usual care and generates less health benefits and is therefore said to be ‘dominated’ by usual care; in the SW the intervention costs less but will be associated with fewer health benefits than usual care; finally, in the SE quadrant the intervention dominates care as usual because it is both less costly and is associated with better health outcomes then enhanced care as usual. Thus, the ICER plane facilitates medical decision-making in a probabilistic way.

The bootstrapped ICERs will also be used to graph the ICER acceptability curve depicting how the probability that the intervention should be regarded as cost-effective depends on the willingness-to-pay per (a) treatment responder, (b) remission, (c) QALY gained.

In addition to the cost-effectiveness analysis (CEA) and cost-utility analysis (CUA), we will also conduct a budget-impact analysis (BIA). In the BIA we will assess the budget impact on the public purse of scaling up the intervention’s implementation, e.g. for scenarios where the intervention covers 20, 40, 60 or the full 100% of the intended target group of people seeking treatment for MDD in later life.

Finally, all health-economic evaluations (CEA, CUA and BIA) will be subject to sensitivity analyses with 20% smaller and 20% larger per-participant intervention cost of the add-on cognitive training. This will be done to ascertain the robustness of the main analyses.

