**Methods:**

In the current multicenter randomized controlled trial (RCT) with a between-subjects design participants aged 60 years and over with a current LLD receiving treatment as usual (TAU) are randomized to add-on CCT or placebo training. Randomization is stratified by depression severity. Participants will receive eight online CCT or placebo sessions spread across four consecutive weeks. They will complete a post-training assessment after 1 month and three follow-up assessments scheduled three, six and 12 months after completing the training. We expect CCT and TAU to be more (cost-)effective in reducing depressive symptoms than placebo training and TAU. Additionally, we will be looking at secondary clinical, cognitive and global functioning outcomes and likely mechanisms of change (e.g., improved cognitive functioning, reduced rumination, and improved inhibition of negative stimuli).

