## Methods

### Design

Our study comprises a single blind RCT with a between-subjects design and two conditions. Participants are randomly allocated to the intervention condition (CCT) or the active control condition (placebo training). Qualitative interviews will be conducted in two subgroups of participants in the intervention arm.

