### Procedure

#### Recruitment, baseline assessment and randomization

A depression experience expert (author PO) provided input on the intervention and application procedure before the start of the trial. The recruitment and assessment process is illustrated in a flowchart shown in Fig. 1. Clinicians will provide eligible candidates with basic information about the study on paper and/or through an informative video. Clinicians will only inform patients capable of consenting to participation. Interested candidates are referred to the researchers who will provide further information by phone. Eligible participants will be asked to provide their written and informed consent for participation at their first visit to the treatment site, where they will subsequently complete the baseline assessment (T0) gauging depressive symptoms, cognitive functioning, rumination, cognitive emotion regulation, quality of life, and health-care consumption, and health-related disability (economic evaluation). If inclusion criteria are satisfied, participants are randomly assigned to the intervention (CCT) or the active control condition (placebo training) by computer-generated allocation stratified for depression severity as assessed with the Inventory of Depressive Symptomatology Self Report: mild (IDS-SR < 38), moderate (IDS 39–48) and severe (IDS > 49) [52]. At the end of the baseline assessment, all participants are provided with a digital tablet to enable them to complete the eight training sessions in their own homes. Researchers will explain, demonstrate and practice the use of the tablet and schedule the training sessions together with the participant. During the one-month training period, participants will receive email notifications to remind them of the task, while researchers will regularly contact them by phone to monitor their progress, with the number and timepoint of the telephone contacts being documented for each participant.

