#### Placebo training

Participants in the control group will be presented with an active placebo training whose duration, frequency and presentation matches the actual CCT. However, participants will only be asked to tap the number on the touch screen that corresponds to the last heard digit, thus not loading working memory. Research has shown this to be a reliable control condition for the active CCT intervention [35].

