The results from the flanking implementation study will serve to inform a wider implementation of digital interventions targeting this growing population within and outside mental-health care, potentially lowering the need for more expensive face-to-face health services. Since the target demographic will become increasingly familiar with digital technologies, computerized interventions will become increasingly relevant, a trend which has been amplified by the COVID-9 pandemic and its ensuing lock-downs. In the implementation study, we will schedule qualitative interviews and focus group meetings to evaluate the appropriateness, acceptability and referral of online CCT. The goal of the implementation study is sustainable later scale up of the CCT intervention. Previous results on the acceptability of digital CCT formats in this population were promising [6], but findings were often obtained in smaller pilot studies. The data we will be collecting will not only support an adequate implementation of the intervention under study but also offer insight into the acceptability and practical implications of digital interventions in general.

Despite the strengths of the trial, there are some limitations. First, there is no control group that receives only treatment as usual to monitor the natural course of depressive symptoms. Both groups follow a form of CCT – active or placebo. Therefore, the results of this trial will not be able to compare CCT treatment to TAU alone. Second, most patient will likely be treated within specialized mental healthcare centers, which limits the generalizability of the results.

In conclusion, new treatment strategies for late-life depression are urgently needed and we hope that, if proven effective, feasible and cost-effective, the intervention will be added to (inter)national guidelines as a recommended add-on to current depression treatment for older adults.

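### The ICER-plane rule states dominance over usual care, but the only randomised comparator is placebo training plus TAU

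*Protocol article*

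**What the plan says.** **The design.** The abstract says that participants "receiving treatment as usual (TAU) are randomized to add-on CCT or placebo training", and the Design section confirms two conditions, CCT and an active control. The control arm is an "active placebo training whose duration, frequency and presentation matches the actual CCT".

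**The hypothesis.** The abstract frames the economic question against that arm: "We expect CCT and TAU to be more (cost-)effective in reducing depressive symptoms than placebo training and TAU". The opening of the Discussion describes the same comparison.

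**The interpretation rule.** The Health-economic evaluation section gives a reading for each quadrant. For the south-east it says that "in the SE quadrant the intervention dominates care as usual because it is both less costly", and the sentence closes by comparing health outcomes with an 'enhanced' form of usual care. For the north-west it calls the intervention dominated by usual care, having used the 'enhanced' label earlier in the same clause. The north-east statement uses the 'enhanced' label only, and the south-west statement uses plain usual care only.

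**The stated limitation.** The Discussion notes that no group receives TAU only and concludes that "the results of this trial will not be able to compare CCT treatment to TAU alone".

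**The concern.** A cost-effectiveness verdict is a statement about a pair of options. Here the rule that turns the bootstrapped ICERs into a verdict names a different pair from the one randomised. Followed literally, a result mostly in the south-east quadrant would be reported as CCT dominating usual care, a contrast the trial does not observe and the Discussion says it cannot make.

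This matters because cost-effectiveness is the fifth stated aim, a budget-impact analysis is to follow, and the authors hope for inclusion in guidelines if the intervention proves cost-effective. A payer deciding on CCT chooses between CCT added to TAU and TAU without it; placebo training is not on offer. That payer would take a published claim of dominance over usual care as the answer to exactly that choice.

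**Working it through.** The plan gives no figure on this point, so the check sets its statements side by side and then asks whether the difference in comparator could alter a verdict.

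**Step 1: the comparator in each place.**

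| Place in the protocol article | Comparator named |
|---|---|
| Abstract, Methods | placebo training and TAU |
| Design | active control (placebo training) |
| Discussion, opening | TAU with a placebo intervention |
| ICER plane, NE | *enhanced usual care* |
| ICER plane, NW | *enhanced usual care*, then *usual care* (the dominance verdict) |
| ICER plane, SW | *usual care* |
| ICER plane, SE | *care as usual* (the dominance verdict), then *enhanced care as usual* |
| Discussion, limitations | no comparison with TAU alone is possible |

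The four quadrant statements name a comparator six times (1 + 2 + 1 + 2). Three of these carry 'enhanced', which is not defined; three are plain usual care. None mentions placebo training. Both dominance verdicts use the plain form.

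**Step 2: what separates the two contrasts.** For costs and for effects alike,

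(CCT+TAU − TAU) = (CCT+TAU − placebo+TAU) + (placebo+TAU − TAU).

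The trial observes only the first term on the right. The second cannot be taken as nil by design: the placebo training matches CCT in duration, frequency and presentation, and "all participants are provided with a digital tablet to enable them to complete the eight training sessions in their own homes". Email reminders and telephone contacts are also described without distinction by arm.

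**Step 3: when a verdict carries over.** Write ΔC and ΔE for the observed cost and effect differences, and pC and pE for the unobserved placebo-versus-TAU differences.

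- SE observed (ΔC < 0, ΔE > 0): dominance over TAU needs pC < −ΔC **and** pE > −ΔE.
- NW observed (ΔC > 0, ΔE < 0): being dominated by TAU needs pC > −ΔC **and** pE < −ΔE.

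The trial supplies neither pC nor pE.

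**Step 4: illustration.** All values are assumed and none comes from the documents. Take ΔC = −100 cost units and ΔE = +0.02 QALY, which is SE against placebo plus TAU. The contrast with TAU is then (−100 + pC, 0.02 + pE):

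| pC | pE = −0.03 (effect −0.01) | pE = 0 (effect +0.02) | pE = +0.02 (effect +0.04) |
|---|---|---|---|
| 0 (cost −100) | SW | SE | SE |
| 50 (cost −50) | SW | SE | SE |
| 100 (cost 0) | equal cost, worse effect | equal cost, better effect | equal cost, better effect |
| 150 (cost +50) | NW | NE | NE |
| 300 (cost +200) | NW | NE | NE |

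One observed SE result is compatible with any quadrant against usual care. The table shows only that the inference does not follow. It does not estimate how likely each outcome is.

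**The case against.** The best defence is that this is loose labelling in a generic account of how to read an ICER plane. The comparison is stated correctly elsewhere, the limitation is disclosed, and 'enhanced' usual care may well have been meant as TAU plus the placebo training. Much of this stands. The ICERs come from the two randomised arms, so no outcome, bootstrap or test is affected. The defence does not rescue the rule as written, because 'enhanced' is undefined, alternates with the plain term inside single sentences, and is absent from both dominance verdicts.

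A reader might infer more, and three such inferences are not supported.

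- **That the economic evaluation is invalid.** It is valid for CCT plus TAU against placebo training plus TAU.
- **That placebo costing is wrong, or that the planned analysis with "20% smaller and 20% larger per-participant intervention cost of the add-on cognitive training" tests nothing.** The article does not say how placebo delivery is costed. That detail may sit in a fuller plan, and its absence here is not an error. The documents also give no delivery cost or QALY gain from which to size the matter.
- **That the bias has a known direction.** If sham training helps, the trial understates the effect of CCT against TAU, which is conservative. If placebo delivery adds cost to the control arm, the trial understates the extra cost of CCT, which is favourable to it. In the illustration, dominance over usual care is lost only if the assumed placebo cost reaches the assumed saving or sham training does harm greater than the observed gain. Neither is documented.

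**Conclusion.** The point holds as a contradiction within the protocol article. The interpretation rule prespecifies two dominance verdicts against usual care, while the design supplies only placebo training plus TAU and the Discussion rules out a comparison with TAU alone.

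Its extent is four quadrant statements, none naming the randomised comparator, with both dominance verdicts worded against an arm that does not exist. No numerical size can be given, because the error moves no estimate; it changes what may be concluded from one. This rests on the text alone. The illustrative values support only the logical step that a verdict against placebo plus TAU need not carry over to TAU.

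The budget-impact text is not itself wrong: it concerns scaling up the intervention and does not say that costs are counted as an increment over placebo. It does invite a reading against current practice, and that reading would be an extrapolation.

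**What to change.** In the Health-economic evaluation section:

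1. Name placebo training plus TAU as the comparator in all four quadrant statements, including both dominance verdicts, and remove the undefined 'enhanced' terms.
2. Add a sentence that no dominance or cost-effectiveness claim over TAU alone will be made from the trial data, consistent with the limitation in the Discussion.
3. State that any conclusion against TAU alone, including a scale-up reading of the budget-impact analysis, will be labelled an extrapolation, with its assumptions about the placebo arm's costs and effects set out.

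The cost is a change of wording and a narrower claim. No new data and no further computation are needed.

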## Discussion

The proposed RCT will examine the (cost-)effectiveness of a cognitive control training (CCT) program as an add-on intervention to specialized depression treatment in adults over 60 years coping with late-life depression (LLD). We will be offering the aPASAT as the active intervention since it targets working memory, which has been found to be effective in reducing depressive symptoms, possibly by increasing cognitive control over repetitive negative thought intrusions. Its effectiveness will be compared to TAU coupled with a placebo intervention (sham training). Change in depressive symptoms, potential working mechanisms, and cost-effectiveness will be investigated post-training and three times during a one-year follow-up. Being a pragmatic trial, inclusion restrictions will be limited, to thus to enhance its ecological validity pertinent to depressed populations in real-world clinical settings.

In addition to change in depressive symptoms, we will study change in rumination and cognitive deficits (i.e., reduced working memory performance) as possible working mechanisms of CCT since both cognitive pathways have been shown to be addressed by the aPASAT [8, 19], with rumination having been identified as a mediating factor between executive dysfunction and depression-related behavior in LLD [63]. We will also be making a first exploration into the effect of CCT on cognitive coping and inhibition of irrelevant (emotional) stimuli to examine the role of these underlying factors of LLD. We will also be looking at age, baseline cognitive control and depression severity to see whether these individual factors affect the effectiveness of CCT differentially and to predict which patients might benefit most from the intervention for well-informed personalized prescription or referral. We also hope to establish whether the addition of CCT to TAU for LLD improves health-related quality of life and overall daily functioning, which often remains impaired even after symptom reduction [14].

From a societal perspective, the cost-effectiveness of mental-health innovations is an important factor. We expect online CCT to reduce healthcare consumption in older adults, while, in and of itself, CCT is an inexpensive treatment. It is readily accessible from home and its standardized format allows easy monitoring and guidance, and systematic comparison of outcomes over time.

The results from the flanking implementation study will serve to inform a wider implementation of digital interventions targeting this growing population within and outside mental-health care, potentially lowering the need for more expensive face-to-face health services. Since the target demographic will become increasingly familiar with digital technologies, computerized interventions will become increasingly relevant, a trend which has been amplified by the COVID-9 pandemic and its ensuing lock-downs. In the implementation study, we will schedule qualitative interviews and focus group meetings to evaluate the appropriateness, acceptability and referral of online CCT. The goal of the implementation study is sustainable later scale up of the CCT intervention. Previous results on the acceptability of digital CCT formats in this population were promising [6], but findings were often obtained in smaller pilot studies. The data we will be collecting will not only support an adequate implementation of the intervention under study but also offer insight into the acceptability and practical implications of digital interventions in general.

Despite the strengths of the trial, there are some limitations. First, there is no control group that receives only treatment as usual to monitor the natural course of depressive symptoms. Both groups follow a form of CCT – active or placebo. Therefore, the results of this trial will not be able to compare CCT treatment to TAU alone. Second, most patient will likely be treated within specialized mental healthcare centers, which limits the generalizability of the results.

In conclusion, new treatment strategies for late-life depression are urgently needed and we hope that, if proven effective, feasible and cost-effective, the intervention will be added to (inter)national guidelines as a recommended add-on to current depression treatment for older adults.

## Data Availability

Not applicable.

## Abbreviations

LLD: Late-life depression
CCT: Cognitive control training
TAU: Treatment as usual
RCT: Randomized controlled trial
NESDO: The Netherlands Study of Depression in Older Persons
CCN: Cognitive control network
dACC: Dorsal anterior cingulate cortex
DLPFC: Dorsolateral prefrontal cortex
(a)PASAT: (adaptive) Paced Auditory Serial Addition Task
DSM-IV: Diagnostic and Statistical Manual of Mental Disorders
M.I.N.I.: Mini International Neuropsychiatric Interview
SCID-I: Structured Clinical Interview for DSM-5
MDD: Major Depressive Disorder
MMSE: Mini-Mental State Examination
IDS-SR: Inventory of Depressive Symptomatology – Self Report
TiC-P: Trimbos Institute and iMTA Cost questionnaire for Psychiatry
COVID-19: Coronavirus disease 2019
RRS: Ruminative Response Scale
BFT: Breathing Focus Task
CERQ: Cognitive Emotion Regulation Questionnaire
RNG: Random Number Generation task
MOCA: Montreal Cognitive Assessment
EQ-5D-5L: EuroQol five-dimensional five-level questionnaire
QALY: Quality-adjusted life-years
WHODAS 2.0: The World Health Organization disability assessment schedule
NoMAD: Normalization MeAsure Development
CONSORT: Consolidated Standards of Reporting Trials
CHEERS: Consolidated Health Economic Evaluation Reporting Standards
ITT: Intention to treat
ICER: Incremental cost-effectiveness ratio
CEA: Cost-effectiveness analysis
CUA: Cost-utility analysis
BIA: Budget-impact analysis
